##### Active range of motion

2.9.2.3

Measuring the active range of motion of a joint is to investigate the influence of the participant's muscle contraction force on the joint activity change values.

##### Barthel index

2.9.2.4

Barthel index is a 3-level evaluation that measures independence in basic activities of daily living following stroke-induced hemiplegia. A normal score is 100. Ability of daily life disorders can be divided into mild (61–99 points), moderate (41–60 points), severe (1–40 points), and completely dependent (0 points).

### Adverse events

2.10

Patients’ legal representatives will be informed of potential adverse events from acupuncture prior to signing the consent form. Any adverse events, including acupoint hematoma, infection, and apostasies, will be recorded by the researchers. In case of severe adverse events occurring, acupuncture intervention will be ceased immediately and proper treatment will be provided. All severe adverse events will be reported to the principle investigator and the ethics committee within 48 hours. Patients will be followed up for 6 month after the trial.

### Data management and monitoring

2.11

Efficacy evaluation and data collection will be carried out by members of the research team other than the operators. The upper limb function of stroke patients was evaluated at the time of enrollment and after each treatment. Researchers managing data will receive training before registration. The evaluator will be responsible for the acquisition of participant information and result evaluation during the study period. First, the evaluator uses the paper version of the evaluation form to record the data, and then enters the data into the excel form for management. The original case report form and all other forms (including the consent form) will be safely archived in the Department of Rehabilitation Medicine, The Second Affiliated Hospital of Chongqing Medical University. Only researchers from our research team can access the final test data.

The composition of data monitoring committee is independent of researchers and has no competing interests; it will check original case report forms, monitor the quality and completeness of data, verify records of adverse events, and ensure that the research complies with the principles of the protocol. Periodic reviews are conducted every 2 months.

### Statistical analysis

2.12

SPSS 26.0 (IBM SPSS, Chicago, IL) will be used to analyze the data. Quantitative data will be presented as mean ± SD. For comparisons of baseline characteristics, the Chi-square test was used for categorical variables, and the Kruskal–Wallis test was used for continuous variables. The characteristics of participants with missing data will be compared between the 2 treatment groups (healthy vs unhealthy outcomes). Inconsistencies will be discussed until a consensus is reached, and further analysis will identify research issues/problems. An independent sample *t* test was used for comparisons of the change in outcome measures between groups. If the data were not normally distributed non-parametric, Wilcoxon and Mann–Whitney *U* tests were applied. The characteristics of subjects without complete follow-up and factors associated with dropout will be analyzed. *P* values of <.05 will be considered statistically significant.

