### Sample size

2.2

The sample size was calculated according to the following formula:

$$\text{N}=\frac{{\left[{\text{u}}_{\alpha }\sqrt{2\text{p}(1-\text{p})}+{\text{u}}_{2\beta }\sqrt{{\text{p}}_{1}(1-{\text{p}}_{1})+{\text{p}}_{2}(1-{\text{p}}_{2})}\right]}^{2}}{{\left({\text{p}}_{1}-{\text{p}}_{2}\right)}^{2}}$$

when the significance level is *α* = 0.05, *β* = 0.10, N is the required sample size for each group. Calculated by the formula: N = 32. There may be the probability of missing to follow-up and termination of various reasons among the subjects. Thus, allowing for 10% to 15% of attrition, the sample size should be adjusted N = 40, that is, each group 40 patients, so the sample size of the 2 groups of patients is determined to be 80 cases.

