### Randomization and allocation concealment

2.6

The randomization sequence will be generated by computer using SPSS 26.0 (IBM, USA). All participants who meet the inclusion criteria will be randomly assigned to an intervention group or control group (40 cases each) at a 1:1 ratio. Opaque computer-generated sealed envelopes will be produced to cover the distribution. The envelope will be serially numbered with a serial number on the outside and will contain distribution information on the inside. Upon completion of baseline assessment and written informed consent, the subject will be enrolled in the study, at which time the envelope will be opened. Participants will be assigned to one of the two groups and receive related interventions. The random distribution sequence and the opaque sealed envelope will be kept separately by 2 specific researchers.

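### Section 2.12 labels the two treatment groups as outcome groups in its missing-data comparison, and its change-score test makes no use of FMA-U readings from patients lost later

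*Protocol article*

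**What the plan says.** **Missing-data comparison (section 2.12).** "The characteristics of participants with missing data will be compared between the 2 treatment groups (healthy vs unhealthy outcomes"), where the parenthesis explains which two groups are meant. Later in the same section: "The characteristics of subjects without complete follow-up and factors associated with dropout will be analyzed".

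**Groups (section 2.6).** Patients are "randomly assigned to an intervention group or control group (40 cases each) at a 1:1 ratio". Section 2.1 describes the same two groups: EA plus routine treatment, and routine treatment alone.

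**Efficacy test (section 2.12).** "An independent sample *t* test was used for comparisons of the change in outcome measures between groups", with rank tests if the data are not normal. The section names no visit, analysis set or rule for missing values.

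**Attrition (section 2.2).** "N is the required sample size for each group. Calculated by the formula: N = 32", and then "allowing for 10% to 15% of attrition, the sample size should be adjusted N = 40".

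**Withdrawal (section 2.13).** Participants who use a prohibited treatment combination, withdraw consent or lose contact are to be excluded from the study. The same section asks the investigator to report reasons for withdrawal and to obtain the time of last treatment and any available outcomes.

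**Visits and blinding.** Section 2.8.4 lists day 0, days 14 and 21, and months 3 and 6. Section 2.7 states that assessors and statisticians are blinded but patients are not.

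**The concern.** The missing-data sentence names two groupings at once. Its main clause points to the treatment groups, and its parenthesis points to outcome groups that the article never defines. An analyst cannot tell which comparison is intended. If it is the parenthesis, there is no FMA-U cut-off with which to form the groups, and the outcome in question may be absent for the patients being classified.

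Loss by arm matters in this trial. Patients know their allocation, follow-up runs to six months, and section 2.8.2 lets a participant leave if the stimulation is not tolerated, a reason that can arise only in the EA arm. Loss could therefore differ between arms in amount and in kind.

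The efficacy test adds to this. A two-sample test on change at one visit needs the baseline value and the value at that visit. Readings taken at earlier post-baseline visits do not enter it, although they carry information about patients lost later. Subtracting baseline is also not the same as adjusting for it as a covariate. Section 2.13 then leaves open whether excluded participants remain in the analysis at all.

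**Working it through.** **1. The two labels side by side.**

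| Source | The two groups |
|---|---|
| Sections 2.1 and 2.6 | EA and control |
| Section 2.12, main clause | the two treatment groups |
| Section 2.12, parenthesis | healthy and unhealthy outcomes |

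The first two rows agree and the third does not. The primary outcome in section 2.9.1 is the FMA-U score (maximum 66), with no threshold that would define a healthy outcome. The error is in the parenthesis.

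**2. The plan's attrition step.** Inputs from section 2.2: 32 per group required, 10% to 15% attrition, 40 per group recruited. The formula is N/(1 − d).

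- d = 0.10: 32/0.90 = 35.6, so 36
- d = 0.15: 32/0.85 = 37.6, so 38
- d = 0.20: 32/0.80 = 40

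The planned 40 lies slightly above the 15% result, so the allowance is adequate. The starting value of 32 cannot be reproduced, because the section gives no values for the two proportions in its formula.

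**3. Completers.** 40 × 0.90 = 36 and 40 × 0.85 = 34 per group, which is 72 to 68 of 80, or 8 to 12 patients lost. Both 36 and 34 exceed 32.

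**4. Power.** Section 2.2 gives no effect in SD units and no sidedness. Assume a two-sided 5% test and the standardised difference that has 90% power at 32 per group: (1.960 + 1.282) × √(2/32) = 0.81 SD. Power at n per group is Φ(0.81 × √(n/2) − 1.960).

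- n = 34: 92%
- n = 36: 93%

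The planned size absorbs the expected loss.

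**5. Possible bias, as an illustration.** Suppose a fraction d of one arm is lost and those patients differ from that arm's full mean by g SD. The completers' mean then shifts by d × g/(1 − d). The values of g are assumptions; nothing in the article supplies them.

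| d | g = 0.25 | g = 0.5 | g = 1.0 |
|---|---|---|---|
| 0.10 | 0.03 SD | 0.06 SD | 0.11 SD |
| 0.15 | 0.04 SD | 0.09 SD | 0.18 SD |

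This shift carries over in full to the between-arm difference only if loss in the other arm is unselective. If both arms lose the same fraction with the same profile, the shifts cancel.

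**6. Data left unused.** There are four post-baseline visits. If FMA-U is recorded at each (Table 1 is not reproduced in the text at hand), a patient lost after day 21 has two post-baseline readings and one lost after month 3 has three. A test on month-6 change uses none of them. A repeated-measures model uses all of them.

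**The case against.** Several stronger readings are tempting, and the article does not support them.

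- *This is the sole missing-data check.* It is not. Section 2.12 also plans to analyse incomplete follow-up and factors associated with dropout, and section 2.13 collects reasons for withdrawal. Neither mentions arm, however, so neither repairs the faulty sentence.
- *The plan replaces EA vs control with an outcome comparison.* The main clause does say treatment groups. This is a contradiction within one sentence, and correcting the parenthesis cures it.
- *The comparison could never be run.* A patient lost late may have earlier scores, so some classification might be possible. The obstacle that remains is that no classification is defined.
- *Everyone with a missing visit is dropped.* Section 2.12 states neither complete-case analysis nor imputation. A t test can be run on imputed values, and such rules are commonly left to an SAP, which is not shown. Their absence is not held against the article.
- *Section 2.13 removes patients from the analysis.* It excludes them from the study but also asks for their outcomes. It does not say which rule governs the analysis set.
- *The type I error is inflated by a known amount.* That would need the split of loss between arms and the dropouts' difference from completers. The article gives neither.

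It is also fair to say that a mixed model recovers little from a patient who leaves before day 14 with only a baseline score, and that the article describes the trial as a pilot. Both points limit the gain. They do not justify leaving the label wrong or the collected readings unused.

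**Conclusion.** The labelling error is certain and rests on the text alone: the parenthesis in section 2.12 conflicts with sections 2.1 and 2.6 and with its own main clause. The second part is a weakness in the stated method: a two-sample test on change uses neither intermediate FMA-U readings nor baseline FMA-U as a covariate, while section 2.13 leaves the place of excluded participants unclear. Lost power is not at stake. Possible bias is, and its size is unknown. The range of 0.03 to 0.18 SD depends wholly on assumed differences of 0.25 to 1.0 SD and on selective loss in one arm only. The change is worth making because it corrects a false statement and uses data the trial already plans to collect.

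**What to change.** 1. In section 2.12, replace the parenthesis with EA vs control. Report the dropout rate and reasons by arm.
2. Estimate the FMA-U effect with a mixed model for repeated measures on all randomised patients, with terms for group, visit, group × visit and baseline FMA-U × visit. Read the group difference at the visit declared primary.
3. Reconcile section 2.13 with that analysis set: state whether participants excluded from the study keep their collected readings in the analysis.
4. Optionally, add a sensitivity analysis in which the imputed values of EA dropouts are worsened in steps.

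The cost is a few lines in sections 2.12 and 2.13. SPSS, the package already named, can fit the model, and no extra visits or patients are needed. The downside is slightly more modelling assumptions than a t test requires. The model does not remove bias from loss that depends on unobserved outcomes, which is the reason for the optional fourth step.

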**Methods::**

A total of 80 IS patients with single upper limb motor function impairment will be recruited in the trial and randomized into EA or control groups. Patients in the control group will receive routine conventional treatment alone while patients in the EA group will receive EA treatment for 3 consecutive weeks based on routine conventional treatment. Baseline evaluation was carried out on day of enrollment, post-treatment evaluation was carried out 14 and 21 days after enrollment, and the 2 groups were follow-ups in 3 and 6 months after the end of the trial. The efficacy will be assessed with the changes in the upper limb Fugl–Meyer assessment, Wolf motor function test, action research arm test, active range of motion, and Barthel index. The safety of EA will be estimated by monitoring the incidence of adverse events and changes in vital signs during the study period. Analysis of feasibility will be descriptive and the change in outcome measures between groups will be analyzed using an independent sample *t* test.

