### Participant recruitment

2.5

Patients who meet our eligibility criteria will be screened consecutively from Department of Rehabilitation Medicine, The Second Affiliated Hospital of Chongqing Medical University. Researchers will screen the list of patients every other day, continue to recruit and monitor recruitment. Eligible patients will be screened, oral and written information about the study will be obtained from the researchers later. After signing the informed consent form, demographic and clinical characteristics will be measured (baseline assessment, t0). Weekly recruitment statistics will be discussed to improve the recruitment process. On this basis, if necessary, the research team discussed updates to recruitment and retention strategies.

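### The t test on change in FMA-U forgoes the extra precision of baseline adjustment, and the normality switch lets the data decide between a mean and a rank comparison

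*Protocol article*

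**What the plan says.** Section 2.12 (Statistical analysis) states that the independent-samples t "test was used for comparisons of the change in outcome measures between groups". The Methods part of the abstract says the same: "the change in outcome measures between groups will be analyzed using an independent sample". Neither place names a baseline covariate. The rule is written for all outcome measures, so it governs the primary outcome, FMA-U (section 2.9.1).

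Section 2.12 then makes the test conditional on the data: "If the data were not normally distributed non-parametric, Wilcoxon and Mann–Whitney" U tests are applied instead. On the threshold it says that P "values of <.05 will be considered statistically significant".

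A baseline FMA-U will be available for this analysis. Section 2.5 says that "demographic and clinical characteristics will be measured (baseline assessment, t0"). That sentence does not name FMA-U, but the abstract and section 2.8.4 place an evaluation on the day of enrolment, and section 2.11 says that upper limb function is assessed then. Section 2.6 has the envelope opened only after the baseline assessment is complete.

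**The concern.** Two features of the stated method deserve attention.

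First, the baseline enters the comparison only by subtraction. That is the same as regressing follow-up on baseline with the slope held at 1. The slope that minimises variance is ρ × SD(follow-up)/SD(baseline), which is usually below 1. When it is, the change score over-corrects, and the estimate is noisier than it need be. In a trial of 80 that lists sample size among its own limitations (section 3), precision that costs nothing is worth taking.

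Second, the t test concerns a difference in mean change, in FMA-U points. The Mann–Whitney test concerns a rank comparison. Under the stated rule, the observed distribution decides which of these is the primary inference.

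**Working it through.** **The plan's own figure.** Section 2.2 sets α = 0.05 and β = "0.10, N is the required sample size for each group", and reports "Calculated by the formula: N = 32". This comes from a two-proportion formula whose p1 and p2 are not given, so 32 can be neither reproduced nor refuted. On attrition, 32/0.90 = 35.6 (36) and 32/0.85 = 37.6 (38). The stated 40 corresponds to 32/0.80, which is 20% attrition. Nothing here supplies an SD or a correlation for FMA-U, so the check below is relative.

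**Inputs.** The documents give 40 per group, 1:1 allocation, a t test on change and no covariate. Two inputs are assumed: equal baseline and follow-up SDs (σ), and a baseline-to-follow-up correlation ρ, shown over a range.

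**Variance per patient, common factor 2/n dropped.**
- Follow-up score only: σ²
- Change score: 2σ²(1−ρ)
- ANCOVA: σ²(1−ρ²)
- ANCOVA relative to change score: (1−ρ²)/[2(1−ρ)] = (1+ρ)/2

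| Assumed ρ | Change vs follow-up only, 2(1−ρ) | ANCOVA vs follow-up only, 1−ρ² | ANCOVA vs change, (1+ρ)/2 | ANCOVA n per group matching 40 by change score | ANCOVA power where change score has 80% | Same, where change score has 90% |
|---|---|---|---|---|---|---|
| 0.5 | 1.00 | 0.75 | 0.75 | 30 | 89.9% | 96.3% |
| 0.7 | 0.60 | 0.51 | 0.85 | 34 | 86.0% | 94.0% |
| 0.8 | 0.40 | 0.36 | 0.90 | 36 | 84.0% | 92.7% |
| 0.9 | 0.20 | 0.19 | 0.95 | 38 | 82.0% | 91.4% |

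The power columns use the normal approximation at two-sided 0.05, with the standardised effect multiplied by √[2/(1+ρ)]. For ρ = 0.5: (1.960 + 0.842) × 1.155 − 1.960 = 1.275, which gives 89.9%.

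**Without equal SDs.** Write σb for the baseline SD and σf for the follow-up SD. Change-score variance minus ANCOVA variance is σf² + σb² − 2ρσfσb − σf²(1−ρ²) = (σb − ρσf)². This is never negative, so in large samples ANCOVA is at least as precise. It is zero when ρσf = σb, which can happen with ρ below 1 if follow-up scores are more spread out than baseline scores.

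**The switch.** Section 2.12 names no normality test. As an assumed version, a 5% Shapiro–Wilk check in each arm followed by the t or Mann–Whitney test was simulated under the null. There were 20,000 replicates at 34 and 40 per arm, with normal, gamma, exponential and t(3) data.
- Type I error of the two-stage rule: 4.6% to 5.3%.
- Type I error if an analyst took the smaller of the two P values: 5.8% to 7.0%.
- Frequency of switching when the data are exactly normal: about 10%.

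**The case against.** The other side has a good deal of force, and most of it limits how strongly the point can be put.

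- **A reader might infer that the baseline information is thrown away.** It is not. At ρ = 0.9 the change score already brings the variance down to 0.20 of a follow-up-only comparison, against 0.19 for ANCOVA. Section 2.3 requires onset more than 6 months earlier, so a high ρ is plausible, though undocumented. Mixed severity at entry would tend to raise ρ and shrink the loss further.
- **A reader might infer that the test is biased, or that baseline imbalance is likely.** Randomisation makes the change-score comparison unbiased, and chance imbalance is covered by its type I error. With 40 per arm the standard error of the baseline difference is √(2/40) = 0.22 SD. A gap of at least 0.25 SD has about a 26% chance and one above 0.5 SD about 2.5%. Adjustment helps in those cases, but nothing shows that they are to be expected.
- **A reader might infer that the switch inflates false positives.** Applied mechanically it hardly does. The 5.8% to 7.0% figure needs an analyst who picks the smaller P value, which the plan does not say will happen. The normality criterion itself may properly sit in an analysis plan that is not shown, so its absence is not the complaint.
- **A reader might infer that only a rank P value would be reported after a switch.** Section 2.12 says quantitative data are presented as mean and SD, so group means would still appear.
- **The study is described as a pilot** (sections 2.14 and 3), which softens an argument from power, though section 2.2 does set a power target.

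What remains is that a stated method can be improved at no cost, and that the type of primary inference is left to the data.

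**Conclusion.** The point holds as an improvement in efficiency and in fixing a single target of inference. It does not show an invalid analysis. The variance saved is 25%, 15%, 10% and 5% at ρ = 0.5, 0.7, 0.8 and 0.9, and the lower end is the more plausible in this population. These figures rest on equal baseline and follow-up SDs and on assumed correlations, because the documents give neither. That adjustment is at least as precise in large samples does not depend on the equal-SD assumption. The objection to the switch is that it makes the primary inference either a mean difference or a rank comparison according to the observed data. Its effect on type I error is negligible if it is applied as a fixed rule.

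**What to change.** Reword section 2.12, and the matching sentence of the abstract, as follows.

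1. The primary analysis is a linear model of FMA-U at the primary visit on treatment group and baseline FMA-U. Report the adjusted mean difference with a 95% CI based on robust standard errors. The estimate still reads as a between-group difference in change, because using change as the response with the same covariate gives the same group effect.
2. Delete the normality-triggered switch. Keep Mann–Whitney on change as a fixed sensitivity analysis, reported whatever the distribution looks like.
3. Analyse each secondary scale in the same way, with its own baseline as covariate.

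The cost is a few lines of text. No new data, visits or patients are needed, the model can be fitted in the package already named (SPSS 26.0), and the baseline measurement is already scheduled.

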### Withdrawal and dropout

2.13

According to the Declaration of Helsinki, all participants will be respected and can withdraw from the study at any time for any reason. Personal information about participants will be collected and kept confidential. Participants will be excluded from the study if they use a treatment combination prohibited by the study protocol, withdraw their consent, or stop communicating. The investigator will report on the withdrawal and the reasons for the withdrawal and obtain measures of the time of the last treatment and possible outcomes.

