### Blinding

2.7

Each participant was initially interviewed and evaluated by a clinician, and the evaluation was then confirmed by another well-trained and experienced clinician. The evaluators, outcome assessors, and statisticians will be blinded to the group allocation and all of them will work independently and separately. It is a pity that patients could not be blinded in this study.

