#### Treatment group

2.8.2

Figure 2 shows the schematic sites of acupuncture points in EA group. Sterilized needles (the acupuncture needles of 0.30 mm in diameter and 25 mm in length [Suzhou Hualun Medical Appliance Co. Ltd., China]) will be used. Acupuncture is inserted vertically, inserted at a depth of about 0.1 to 0.3 cm, and the electrical stimulation device is connected after Deqi sensation. The parameters were selected as follows: 20 Hz square wave, current intensity 0.5 mA, each lasting 30 seconds, stimulating once every 5 minutes. The participant could withdraw from the trial if he could not tolerate the stimulation. Stimulation was performed for 30 minutes per day for 3 consecutive weeks.

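### Section 2.13 takes randomised patients out of the study, not only off treatment, for using a prohibited treatment, so the comparison may no longer be between the groups as randomised

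*Protocol article*

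**What the plan says.** Section 2.13 (Withdrawal and dropout) sets one consequence for three events: "Participants will be excluded from the study if they use a treatment combination prohibited by the study protocol, withdraw their consent, or stop communicating". The exclusion is from the study, not from treatment. The next sentence has the investigator report the withdrawal and its reasons and "obtain measures of the time of the last treatment and possible outcomes".

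Section 2.8.2 (Treatment group) adds, for electroacupuncture (EA): "The participant could withdraw from the trial if he could not tolerate the stimulation".

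Section 2.7 (Blinding) says that "patients could not be blinded in this study", and also that "The evaluators, outcome assessors, and statisticians will be blinded to the group allocation".

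Section 2.12 (Statistical analysis) gives the main comparison as an independent-sample t test; this "test was used for comparisons of the change in outcome measures between groups". On incomplete data it says: "The characteristics of subjects without complete follow-up and factors associated with dropout will be analyzed". It also plans to compare the characteristics of participants with missing data between groups.

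Section 2.8.4 (Follow-up) schedules assessments at day 0, days 14 and 21, and 3 and 6 months. Section 2.9.1.1 has the primary outcome, the upper limb Fugl–Meyer assessment (FMA-U), measured 6 months after the intervention.

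**The concern.** Withdrawn consent and lost contact are losses that the trial cannot prevent. Use of a prohibited treatment is different: the patient is usually still reachable and willing to be assessed, and it is the protocol that ends participation.

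Such use is unlikely to be independent of arm and outcome. Controls know that they receive routine rehabilitation alone, and one who recovers poorly has a reason to look elsewhere. An EA patient who sees no benefit may do the same. Follow-up runs for months after the three-week treatment, which leaves time for this. If these patients leave the study, those left in each arm have been selected by events after randomisation, and a t test on their change scores has no protection against that.

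The intolerance sentence in section 2.8.2 is a lesser, related point. Only EA patients receive stimulation, so only they can meet the condition, and the option is worded as leaving the trial when stopping stimulation would be enough.

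What is at stake is the scheduled later FMA-U data. A statistical analysis plan can name an intention-to-treat set, but it cannot recover 3- and 6-month scores that were never collected because the protocol had excluded the patient.

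**Working it through.** **The passages side by side**

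| Question | What the article says |
|---|---|
| Does prohibited-treatment use end treatment or participation? | Participation (2.13) |
| Is anything measured at exit? | Yes: measures around the last treatment, and possible outcomes (2.13) |
| Are the later scheduled visits kept for these patients? | Not stated |
| Do the exit data enter the comparison? | Not stated |
| What is done about incomplete follow-up? | Characteristics and factors associated with dropout are examined (2.12) |
| Who is unblinded? | Patients; assessors and statisticians are blinded (2.7) |

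The first row is a stated rule. The remaining rows do not undo it.

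**Illustration of size**

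The plan gives no figure for losses under this rule, so there is none to reproduce. The 32 per group in section 2.2 cannot be checked, because the two proportions are not given, and this point does not depend on it.

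Inputs from the document: 40 patients per group (2.2, 2.6), significance level 0.05 (2.2, 2.12), and an attrition allowance of 10% to 15% (2.2).

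Assumptions, not in the document: there is no true effect; one arm loses a fraction *f* of 10% or 15%; those lost have a mean change *g* of 0.5 or 1.0 SD below those who remain; the other arm loses nobody; the test is two-sided and treated as normal.

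Formulas:

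- Bias in the mean of the arm with losses: *b* = *f* × *g*
- Standard error in SD units: SE = √(1/(40(1 − *f*)) + 1/40)
- Rejection rate: P(|Z + *b*/SE| > 1.96)

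For *f* = 10%, 36 remain and SE = √(1/36 + 1/40) = 0.230. For *f* = 15%, 34 remain and SE = √(1/34 + 1/40) = 0.233.

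| *f* | *g* (SD) | *b* (SD) | *b*/SE | Two-sided error |
|---|---|---|---|---|
| 10% | 0.5 | 0.050 | 0.218 | 5.5% |
| 15% | 0.5 | 0.075 | 0.322 | 6.2% |
| 10% | 1.0 | 0.100 | 0.435 | 7.2% |
| 15% | 1.0 | 0.150 | 0.643 | 9.9% |

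The result depends on how the gap is defined. If *g* is measured from the mean of the whole arm, the bias is *f* × *g*/(1 − *f*). The two ends of the table become 0.056 SD with 5.7% error and 0.176 SD with 11.8% error.

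**If both arms lose poor responders**

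The biases then oppose each other. Take the worst row (15%, 1.0 SD) in one arm.

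- Other arm loses 10% with a gap of 0.5 SD: net bias 0.150 − 0.050 = 0.100 SD, SE = √(1/34 + 1/36) = 0.239, error 7.0%.
- Other arm loses 10% with a gap of 1.0 SD: net bias 0.150 − 0.100 = 0.050 SD, error 5.5%.
- Equal losses with equal gaps: net bias 0, error 5.0%.

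**The case against.** The strongest reply is that section 2.13 excludes patients from the study and never says that they are excluded from the analysis. Measures are to be taken at exit, dropouts are to be examined, and a condensed article may leave analysis sets to a fuller document. This stands in part. The absence of a named intention-to-treat set is not the fault here, and it is not established that every such patient would be missing or that the data would be discarded. It does not remove the point, because ending participation is a rule about data collection, and exit measures do not replace the scheduled 3- and 6-month assessments.

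Several stronger readings are tempting but are not supported:

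- *Patients are removed for intolerance.* Section 2.8.2 says that the participant could withdraw. That is a permitted exit, and section 2.13 already lets anyone in either arm withdraw for any reason.
- *The trial is open-label throughout.* Only patients are unblinded. Assessor blinding protects the scoring, but it does not prevent selective loss.
- *Safety rates are biased too.* Section 2.10 records any adverse event and follows patients for 6 months. Nothing says that events before exit are dropped.
- *The bias can be set against the effect the trial can detect.* The article gives no detectable difference on FMA-U; it sizes the trial on two proportions that it does not report.

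It is also fair to say that the illustration places the whole all-cause attrition allowance in one arm and makes all of it depend on outcome. The article gives no expected frequency of prohibited-treatment use, so the real fraction may be small. The study also calls itself a pilot, which lowers the stakes somewhat, although it tests at the 5% level and says that it will give solid evidence.

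**Conclusion.** The point holds for the prohibited-treatment clause of section 2.13. As written, it turns a protocol deviation after randomisation into an exit from the study. With unblinded patients, that exit can depend on arm and on recovery. The intolerance sentence in section 2.8.2 is a secondary wording problem confined to the EA arm.

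Neither the size nor the direction of the bias is known. The range of 5.5% to 9.9% rests on one-sided, outcome-dependent loss at the full attrition allowance, and three of its four scenarios lie at 7.2% or below. If both arms lose poor responders, the error moves back towards 5%. The attrition allowance adds patients but does not remove this bias.

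This should be fixed. The unknown frequency and the planned exit measures keep it from being graver. What makes it worth acting on is that assessments lost under the rule cannot be recovered at analysis.

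**What to change.** Reword section 2.13 and the sentence in section 2.8.2 along these lines:

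> Use of a prohibited treatment is recorded as a protocol deviation, and stopping EA as treatment discontinuation. In either case the consenting patient remains in the study, is assessed at all scheduled visits and is analysed in the randomised group. Follow-up ends only if the patient withdraws consent to data collection or contact is unavoidably lost, and data up to that point are kept and used.

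Make the comparison of all patients as randomised the primary one, and keep the set without deviations as a sensitivity analysis. Clinical decisions on when stimulation is stopped stay as they are.

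The cost is a change of wording and outcome visits, already in the schedule, for what may be a few patients. There is a small downside: the estimate will include non-adherence and co-treatment and may be slightly diluted.
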